## Abstract

**Introduction:**

Despite the high prevalence of chronic low back pain (cLBP), its underlying mechanisms remain poorly understood. Addressing modifiable psychosocial resources and health behaviours such as physical activity offers a promising avenue for reducing the impact of cLBP. Furthermore, although the relationship between physical activity and pain is theorised as a within-person process, previous research has primarily focused on between-person differences. In this article, we present the protocol for the prospective observational study PRIA (Psychologie und Rückengesundheit im Alltag), which is part of a larger interdisciplinary research consortium investigating preventive, diagnostic and therapeutic aspects of cLBP. Drawing on theories from health and pain psychology, the outlined study examines the interplay between different dimensions of cLBP and back health, physical activity and their psychosocial determinants within individuals in their everyday lives.

**Methods and analysis:**

This prospective longitudinal study combines online questionnaires with ecological momentary assessment of health behaviours, cognitions, affect, social support and pain using a smartphone-based app (movisensXS) and continuous measurement of physical activity by accelerometry (movisens Move 4). Parameters will be recorded at baseline (T0), daily for the following 14 days (five times per day at 09:00, 12:00, 15:00, 18:00 and 21:00, resulting in up to 70 measurement occasions), 3 and 6 months later (T1 and T2). A total of 230 participants (115 individuals with cLBP and 115 without cLBP) aged 18–64 years will be enrolled. The associations between cLBP and the measured parameters will be examined using multilevel models.

**Ethics and dissemination:**

The university’s ethics committee at the MSB Medical School Berlin approved the study on 8 March 2021 (approval number MSB-2021/59, amendment approved on 10 November 2023, amendment number MSB-2023/145). Ethical approval for the FOR 5177 initial screening was granted by Charité – Universitätsmedizin Berlin (EA1/058/21). All participants provided written informed consent. The results of this research will be published in peer-reviewed international journals, presented at national and international conferences, and reported to the German Research Foundation.

**Trial registration number:**

DRKS00032978.

STRENGTHS AND LIMITATIONS OF THIS STUDYThis study shifts the focus from a pathological perspective to a more resource-oriented approach to chronic low back pain (cLBP), with the aim of preventing cLBP and promoting back health.The study considers psychosocial risk factors and resources alongside biomechanical factors in a cohort of individuals with and without cLBP.Ecological momentary assessment combined with accelerometry allows for high temporal data resolution at the intra-individual level.The observational design of the study precludes conclusions about causality; instead, the study highlights key risk factors and resources for cLBP that should be examined further in interventional studies, for example, in the form of just-in-time adaptive interventions.

## Introduction

 Low back pain (LBP) is a health complaint responsible for the most years lived with disability worldwide.^1^ A population-based study from Germany showed that 52.9% of adults had experienced LBP in the past year, with 15.5% of this cohort reporting back pain for at least 3 months, referred to as chronic back pain.^2^ Despite the high prevalence of chronic LBP (cLBP) and its substantial contribution to work-related disability,^3^ understanding of the aetiology of cLBP and its successful prevention remains limited. Recent research suggests that targeting modifiable behaviour-related risk factors such as smoking, high body mass index (BMI) and low physical activity could substantially reduce the number of years lived with disability due to cLBP.^1 4^ This emphasises the importance of prioritising health behaviours such as physical activity in the prevention and treatment of cLBP. Therefore, this study aims to examine patterns of physical activity and their linkages with cLBP. Additionally, we aim to identify psychosocial predictors of pain, back health and physical activity, grounded in behaviour change theory, to inform the development of behavioural interventions.

### The role of psychosocial factors and physical activity in cLBP

According to the biopsychosocial model of LBP,^5^ cLBP is considered a multidimensional syndrome. Often, the persistence of pain is not directly related to the factors that contributed to the initial onset of pain, such as injury or overuse, but rather to the factors that maintain the pain. As non-specific LBP (ie, back pain without a clear organic origin) persists, psychological, behavioural and social risk factors may contribute to its progression to cLBP.^6 7^ Similarly, a growing body of literature shows that the subjective experience of pain (eg, pain intensity) is highly dependent on psychological risk factors—commonly referred to as ‘yellow flags’. These include, for example, perceived stress, negative affect, depressive symptoms and cognitive responses to pain such as catastrophising.^7 8^

In turn, engaging in health behaviour such as physical activity is essential for enhancing overall health and lowering the risk of mortality.^9^ The WHO recommends undertaking regular physical activity, including moderate-to-vigorous intensity physical activity and muscle-strengthening physical activity in a considerable amount throughout the week.^10^ Although physical activity, and leisure-time physical activity (LTPA) in particular,^11 12^ is widely acknowledged as an important non-pharmacological strategy for preventing and managing cLBP, there is inconsistent and limited evidence regarding the most beneficial type, intensity, duration and frequency of LTPA for preventing cLBP.^11 13^

### Understanding the links between pain, psychosocial factors and physical activity: towards a resource-oriented approach to cLBP

While previous research has often focused on risk factors, such as health risk behaviours^1^ or maladaptive cognitions,^8^ the present study takes a more comprehensive approach that includes both risk and protective factors.^14^ Such an approach emphasises that the absence of disease cannot be equated with health and posits that LBP and back health are distinct concepts.^15^

Theoretical perspectives from the psychology of behaviour change and the chronification of pain provide a framework for examining the complex relationships between health or disease, psychological and social factors, and health behaviours. In particular, the back health behaviour model (BHBM)^16^ represents a systematic, theory-based framework that integrates key insights from pain psychology (ie, the fear-avoidance model^17^ and the avoidance-endurance model of pain^18^) and health psychology (ie, the health action process approach, HAPA^19^ and the physical activity adoption and Maintenance^20^). As the BHBM considers both psychological and behavioural resources and risk factors (see figure 1), it is well suited to a comprehensive examination of cLBP and back health.

**Figure 1 F1:**
[figure not shown]
Theoretical framework of the PRIA study: The Back Health Behaviour Model by Wilhelm *et al.*^16^ The figure has been adapted to include biomechanical variables: spine morphology, mechanics and motion (‘The 3 M’s’). PRIA, Psychologie und Rückengesundheit im Alltag.

Taking a closer look at the BHBM,^16^ at the behavioural level, health behaviour such as LTPA can be seen as a resource-oriented coping and prevention strategy. Importantly, successful engagement in health behaviours requires the involvement of explicit and implicit processes at the psychological level. For instance, an individual’s intention to engage in physical activity is determined by their subjective appraisal of their own resources (eg, (pain) self-efficacy, (pain-related) social support), but also by their emotional states (eg, affect) or pain-related beliefs (eg, fear-avoidance beliefs). In turn, if individuals are motivated to adopt behavioural changes, they need to translate their intentions into behaviour using volitional, self-regulatory strategies (eg, planning). Figure 1 shows the BHBM modified to account for contextual and biomechanical factors.

### Capturing fluctuations in pain intensity, back health and physical activity using ecological momentary assessment

Both the experience of pain and related factors often vary over time within individuals.^21^ Thus, multiple assessment designs that aim to capture the temporal dynamics between variables are well suited to examining cLBP. The number of studies investigating cLBP using ecological momentary assessment (EMA) designs has increased over time.^22^ An EMA design can provide new insights into how psychosocial predictors, health behaviours (ie, physical activity), and behaviour-related outcomes (ie, pain intensity, back health) evolve at different levels of temporal resolution and with different time lags, for example, moment-to-moment or day-to-day. This, in turn, allows us to test theoretical assumptions at both the within-person and between-person levels simultaneously.^23^

### The present study

Studies examining the associations between physical activity and pain and its theory-based, modifiable predictors are needed to inform the design of behavioural interventions to prevent cLBP. This prospective observational study PRIA (Psychologie und Rückengesundheit im Alltag) considers both risk factors and resources for cLBP, both in terms of health behaviours (eg, LTPA, back posture and mobility) and psychosocial factors (eg, self-efficacy, positive affect, social support). Importantly, in line with health conceptualisations,^15^ self-reports of LBP are complemented by self-reports of back health to explore the potential utility of health measures in the prevention and treatment of cLBP. Another important aim of the PRIA study is to investigate the intra-individual (ie, within-person) variation in pain, back health and physical activity and its theoretical determinants. In doing so, the study aims to improve our understanding of how the temporal dynamics between LBP and back health evolve in the daily lives of individuals with and without cLBP, and how these within-person patterns differ between individuals with different individual characteristics.

Specifically, the research objectives of the PRIA study are to (a) capture how LBP intensity and back health unfold in daily life, (b) identify physical activity patterns in individuals with and without cLBP, (c) examine the associations between pain intensity, back health and physical activity and (d) identify key modifiable psychosocial correlates of and health behaviours related to pain intensity and back health. While seeking modifiable correlates of cLBP, we will also consider the role of non-modifiable factors. For example, given the accumulating evidence that sex and gender differences are an important source of variation in how individuals experience and respond to pain,^24 25^ we will consider gender to build a comprehensive model.

#### Between-person hypotheses

As physical activity, and LTPA in particular,^12^ has been conceptualised as a key predictor of LBP and back health, as well as mediating the association between psychosocial factors and LBP and back health (figure 1), we propose several hypotheses regarding LTPA. First, we hypothesise that individuals with cLBP will differ in their physical activity patterns from individuals without cLBP. Relatedly, we expect that individuals with cLBP will experience more challenges in regulating their health behaviour (eg, lower intention and poorer self-regulation; figure 1) than participants without cLBP, for example, due to their respective pain-related and physical activity-related cognitions (eg, higher levels of kinesiophobia). Second, we hypothesise that higher average levels of LTPA will be associated with lower levels of pain and better back health, posture and mobility.

With regard to psychosocial factors, we expect that higher levels of pain-related and activity-related cognitions that can be considered risk factors for cLBP (eg, kinesiophobia) will be associated with higher pain intensity and poorer back health, whereas resources (eg, pain self-efficacy) will be associated with lower pain intensity and better back health. On the contextual variables side, we will explore whether higher levels of perceived general and pain-related social support are associated with lower pain intensity and better back health. In collaboration with the overall research consortium, we will also investigate whether and how spinal morphology, mechanics and motion are linked to LBP, back health and physical activity.

In terms of the macrolongitudinal perspective, we expect the variables measured at baseline, 3 months and 6 months after baseline to be relatively stable over the chosen time intervals, as no intervention has been implemented.

#### Within-person hypotheses

At the within-person level, we will examine how changes in psychosocial variables covary with changes in physical activity and subsequently with LBP intensity and back health. We hypothesise that people will report lower pain intensity and better back health at times when they are more physically active in their leisure time than usual. We also expect to observe lower pain intensity, better back health and more LTPA engagement than usual at times when self-control, pain self-efficacy and positive affect are higher than usual, and fear of movement and negative affect are lower than usual.^26^,^29^ We will explore these relationships at different levels of temporal resolution (eg, momentary, daily) and for different time lags (eg, same measurement time, different time points).

## Methods and analysis

### Study design

This observational study uses a prospective macro-longitudinal design spanning 6 months, complemented by a micro-longitudinal phase using EMA over a 14-day period (figure 2). The study is embedded in an interdisciplinary research consortium, FOR 5177,^30^ which is investigating spinal morphology (eg, spinal shape), mechanics (eg, lumbar spinal loading) and motion (eg, spino-pelvic kinematics and physical activity) as well as interventions and mechanisms, and how they are related to and associated with cLBP. The overall goal of the FOR 5177 research consortium is to improve the understanding of the aetiology and pathogenesis of cLBP, to propose novel strategies for patient stratification, and to advance the prevention and treatment of cLBP. To this end, static imaging (ie, magnetic resonance imaging) and short physical assessments, as they represent the current clinical diagnostic approach in cLBP, are complemented by dynamic investigations of spinal mobility and loading, and assessments of physical activity and psychosocial factors in daily life. In the following, we describe the PRIA subproject, including the specific study sample, procedures and measures that contribute to FOR 5177 and can also serve as an independent analysis sample.

**Figure 2 F2:**
[figure not shown]
Study design: The PRIA study is a prospective macro-longitudinal study spanning 6 months, with a 14-day micro-longitudinal EMA phase. EMA, ecological momentary assessment; PRIA, Psychologie und Rückengesundheit im Alltag.

### Sample and recruitment

Adults have been recruited in the greater Berlin area since January 2023. Recruitment methods include local advertising at Charité – Universitätsmedizin Berlin, Humboldt Universität zu Berlin and MSB Medical School Berlin (via postal flyers, notice boards, internet outreach and social media), outreach to the general public (via newspapers, magazines, podcasts, TV), collaboration with local companies and administrative authorities and word of mouth. In addition, the study was promoted during the Long Night of Sciences, a public science fair in Berlin in 2022, 2023 and 2024. Participants are emailed information material and invited for a brief introductory telephone call to explain the procedure, review the inclusion and exclusion criteria and schedule a baseline appointment. After receiving verbal and written information for the PRIA study, including information on the sampling scheme and study devices, participants provide written informed consent.

### Inclusion and exclusion criteria

Participants must meet the following inclusion criteria: (1) report lumbopelvic pain for the past 12 weeks or longer (ie, participants with cLBP), report intermittent lumbopelvic pain or no lumbopelvic pain at all (ie, participants without cLBP), (2) be between 18 and 64 years old, (3) be able to hear an alarm from a smartphone and (4) be able to read and understand German text on a 6-inch smartphone and a 10-inch tablet. In terms of exclusion criteria, participants were also required not to: (1) be enrolled in other ongoing clinical trials, (2) be currently pregnant, (3) be a professional, competitive or top athlete, and (4) have a BMI >28 kg/m^2^. Further exclusion criteria are listed in the FOR 5177 registration in the German Clinical Trials Register (DRKS number: DRKS00027907).

### Procedures

Participants undergo an initial screening at the Charité – Universitätsmedizin Berlin. Each participant in the PRIA subproject then completes a battery of self-administered questionnaires at baseline (time 0, T0), with subsequent follow-up questionnaires (time 1 and 2, T1 and T2; macro-longitudinal design). Data are collected via an online survey platform (Unipark, Tivian XI, Cologne, Germany) using a study tablet on-site (T0) or a personal device at home (eg, computer, tablet, smartphone; T1–T2).

Participants are then instructed in the time-sampling procedure, the use of the Android study smartphone (Nokia 6.3) equipped with the movisensXS app (movisens GmbH, Germany), and the proper handling of the accelerometer (Move 4, movisens GmbH, Germany). For the following 14 days, participants wear the activity sensor to collect data on their physical activity during waking hours. In addition, at five alarm-triggered measurement occasions per day (at 09:00, 12:00, 15:00, 18:00 and 21:00), participants fill out short self-report questionnaires using the study smartphone and the movisensXS app. Each assessment takes approx. 2 min to complete, resulting in a total of 2.5 hours of diary assessments during the entire EMA phase.

At the end of the 14-day period, participants return the study devices and are reimbursed €30 for completing the assessment. On day 16, participants are being emailed a link to a feedback questionnaire about their experience of the EMA phase. Participants then receive individualised feedback on selected EMA variables. At T1 (3 months after T0) and T2 (6 months after T0), participants are again being emailed links to the follow-up questionnaires.

### Benefits and harms

Given the non-invasive nature of both the accelerometer measurements and the online questionnaires, we do not anticipate any harm beyond the time commitment required of participants. In addition, participants were reimbursed €30 and received individualised feedback on selected variables assessed within the EMA.

### Patient and public involvement

Participants are encouraged to report any questions or adverse effects they experience during the study to the study facilitator via text message on the movisensXS app, email or phone call. After the EMA phase, participants are requested to provide feedback on the study to improve future assessments. During the study preparation phase, the researchers consulted the Patient Advisory Board on participants’ feedback and concerns.

### Measures

#### Macro-longitudinal measures

Table 1 provides an overview of the variables measured at T0, T1 and T2. At T0, participants provide information on demographic characteristics, LBP chronicity status, LBP intensity and pain-related disability, back health, physical activity and theory-based psychological variables. Time-sensitive variables are being reassessed at T1 and T2.

**Table 1 T1:** Variables and sampling scheme for the macro-longitudinal study period

Variable	Initial screening*	Baseline (T0)	3 months (T1)	6 months (T2)
Demographic information: Age, gender, marital status, children, living situation, education, job status, income, subjective social status	–	x	–	–
Sex, occupational field, years of work, occupational and family burdens, occupational disability, retirement status	x	–	–	–
**Behavioural outcomes**				
Physical activity and sedentary behaviour: International Physical Activity Questionnaire long version	–	x	x	x
Back posture and mobility: Back Posture, Movement and Mobility self-report questionnaire, Postural Awareness Scale	–	x	x	x
Back posture and mobility (objective): Idiag M360 (Idiag AG, Switzerland)	x	–	–	–
Medication intake: Medication Quantification Scale	–	x	x	x
**Behaviour-related health outcomes with respect to the lower back**				
Low back health: Single item adapted from the SF-36/SF-12 Health Survey	x	–	x	x
Low back pain: Chronic Pain Grade Questionnaire, chronicity of LBP	x	x	x	x
Disability due to low back pain (Roland-Morris Disability Questionnaire)†	x	–	x	x
General physical and mental health: Health-related Quality of Life (SF-36^1^/SF-12 Health Survey^2^)	x^1^	–	x^2^	x^2^
Depressive symptoms and anxiety (Patient Health Questionnaire-4)	x	–	x	x
Perceived Stress Scale (PSS-10)	x	x	x	x
**Theory-based psychological variables**				
Activity-related cognitions: risk perception, outcome expectancies, self-efficacy, intention, planning	–	x	x	x
Habit strength (Self-Report Behavioural Automaticity Index)	x	–	x	x
Back-related and pain-related beliefs: Pain catastrophising (Pain Catastrophising Scale)†, pain self-efficacy (Pain Self-Efficacy Questionnaire)†, Avoidance-Endurance Fast Screen†	–	x	x	x
Fear of movement (Tampa Scale for Kinesiophobia)	x	–	x	x
Social processes: Perceived general social support; responses of others to pain (West Haven-Yale Multidimensional Pain Inventory, Part II)	–	x	x	x
Affect: Positive and Negative Affect Schedule	–	–	x	x
General self-control: Self-Control Scale	–	x	x	x

* The initial screening is not part of this study, but of another subproject within the FOR 5177 research unit—data are available.

† Questions will only be presented to participants who report to currently experience LBP.

LBP, low back pain.

#### Primary outcome

LTPA is the primary outcome variable, assessed as non-work-related moderate-to-vigorous physical activity. Participants complete an adapted version of the validated German version of the International Physical Activity Questionnaire, IPAQ long.^31 32^ The questionnaire covers different intensities of physical activity in four activity domains including housework and gardening, work-related activities, transport, LTPA and sedentary behaviour. Participants report the number of hours and/or minutes spent in moderate and vigorous activities within each activity domain over the past 7 days. The IPAQ data will be processed according to the IPAQ protocol.^33^ The validity of the IPAQ will be evaluated empirically by assessing its agreement with the accelerometer data collected in this study.

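### The IPAQ validity check sets a 7-day recall against sensor data from different weeks, so poor agreement alone cannot be attributed to the questionnaire

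*Protocol article*

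**What the plan says.** The primary outcome is leisure-time physical activity (LTPA), measured at the macro-longitudinal time points with an adapted German IPAQ long form. The Primary outcome section gives the recall period: "Participants report the number of hours and/or minutes spent in moderate and vigorous activities within each activity domain over the past 7 days". It then commits to a validity check: "The validity of the IPAQ will be evaluated empirically by assessing its agreement with the accelerometer data collected in this study". It does not say which IPAQ administration or which sensor days are compared, and it does not mention that the two may cover different periods.

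The timing is set elsewhere in the article:

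- In Table 1, the row "Physical activity and sedentary behaviour: International Physical Activity Questionnaire long version" is marked at T0, T1 and T2, and not at the initial screening.
- In Procedures, the T0 questionnaires are completed first, on site. After that, "Participants are then instructed in the time-sampling procedure" and in the use of the devices.
- Sensor wear comes next: "For the following 14 days, participants wear the activity sensor to collect data on their physical activity during waking hours".
- Wear then stops: "At the end of the 14-day period, participants return the study devices". No further wear is described at T1 or T2.
- One more questionnaire follows: "On day 16, participants are being emailed a link to a feedback questionnaire about their experience of the EMA phase". No IPAQ items are described for it.

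Under the micro-longitudinal measures, the Physical activity section adds that recordings are trimmed to exactly 14 study days.

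**The concern.** Agreement with a reference measure speaks to validity when both instruments describe the same behaviour over the same time. Here they describe different weeks. A participant who reports the week before T0 perfectly, and is then more or less active in the next two weeks, shows up as disagreement. Any change in behaviour caused by wearing a sensor and answering five prompts a day adds to it.

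At stake is what may be concluded about the IPAQ, which carries the primary outcome at T0, T1 and T2. Read as written, the check would count real change between weeks as questionnaire error, and a sound instrument could be reported as performing poorly. An analysis plan can choose the agreement statistic, but it cannot create overlapping days, because the mismatch is fixed by the collection schedule.

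**Working it through.** The article gives no figure for this check, so there is none to reproduce. Two things can be worked out.

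**1. Shared days.** Take T0 as day 0, 3 months as day 91 and 6 months as day 183. The sensor covers days 1 to 14.

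| IPAQ | Recall window (days) | Days shared with sensor | Days from sensor end to start of recall |
|---|---|---|---|
| T0 | −7 to −1 | 0 | recall precedes sensor |
| T1 | 84 to 90 | 0 | 91 − 7 − 14 = 70 |
| T2 | 176 to 182 | 0 | 183 − 7 − 14 = 162 |

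Counting the day of completion as part of the recall (for T0, days −6 to 0) still gives zero shared days. T0 is the closest administration, and its recall is adjacent to the sensor period rather than inside it.

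**2. Best attainable agreement with no measurement error.** Write a person's true weekly activity as a stable person level plus an independent deviation for each week, with total variance 1 and week-to-week ICC ρ. Suppose the IPAQ reports the T0 week without error and the sensor measures its two weeks without error.

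- Covariance of the T0 week with the mean of the two sensor weeks: ρ.
- Variance of the two-week mean: ρ + (1 − ρ)/2 = (1 + ρ)/2.
- Maximum correlation: ρ / √((1 + ρ)/2).
- Variance of the difference: (1 − ρ) + (1 − ρ)/2 = 1.5(1 − ρ).
- 95% limits of agreement: ±1.96 × √(1.5(1 − ρ)) weekly SDs.

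Example at ρ = 0.6: 0.6/√0.8 = 0.67, and 1.96 × √0.6 = 1.52.

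| Assumed ρ | Maximum correlation | 95% limits of agreement (weekly SDs) |
|---|---|---|
| 0.5 | 0.58 | ±1.70 |
| 0.6 | 0.67 | ±1.52 |
| 0.7 | 0.76 | ±1.31 |
| 0.8 | 0.84 | ±1.07 |
| 0.9 | 0.92 | ±0.76 |

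Simulation at ρ = 0.6 and 0.8 gave the same values. If a recall week lay inside the sensor period and were compared with those same 7 days, the maximum correlation would be 1 and the limits of agreement 0.

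**3. What the sensor data can supply.** Under the same model, an error-free T0 recall correlates ρ with sensor week 1, and sensor week 1 correlates ρ with sensor week 2. The second quantity is observable in this study. It therefore estimates how much agreement week-to-week change alone would allow.

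**The case against.** The strongest reply is that the comparison remains informative. Good agreement would support the IPAQ as a measure of habitual activity. In its introduction, the article expects the variables measured at T0, T1 and T2 to be relatively stable, and at an ICC of 0.9 the cap is 0.92, which costs little. Two sensor weeks per person also allow instability to be estimated from planned data, and intraclass correlations are already planned for the micro-longitudinal data. Much of this stands. But the stability expectation is untested and not tied to this check, and within-person variation in activity is itself a study aim. The Primary outcome section also does not say that agreement will be judged against week-to-week stability.

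A reader might infer three stronger claims that the article does not support.

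- *That the validity of the primary outcome rests on this check.* The IPAQ version used is adapted from an already validated one, and no decision is tied to the result. LTPA is also self-reported at each prompt of the EMA phase alongside concurrent accelerometry, and the multilevel models of those data do not depend on the T0 IPAQ.
- *That leisure-only IPAQ minutes will be set against all-domain sensor minutes.* The article does not say so. The IPAQ covers all domains, so totals can be compared. The times of leisure activity and the work hours reported at 21:00 would allow matching. The choice of score is a detail an article may leave to the analysis plan.
- *That poor agreement can never be informative about the questionnaire.* If IPAQ agreement falls well below the agreement between the two sensor weeks, that is evidence of reporting error, apart from any reactivity to monitoring.

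**Conclusion.** The point holds in a limited form. On the article's own schedule, no IPAQ recall day is a sensor day, yet the plan is to evaluate IPAQ validity by agreement between the two. Poor agreement taken alone cannot be attributed to the questionnaire.

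The size depends on how stable weekly activity is. The range of 0.58 to 0.92 for the maximum correlation with the 14-day mean rests on assumed ICCs of 0.5 to 0.9, equal correlation between all pairs of weeks, and error-free instruments. The figures illustrate the mechanism; they do not show that the loss is large in this cohort. The within-person analyses of EMA-reported LTPA are not affected. What changes is the conclusion that may be drawn about the IPAQ.

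**What to change.** In the Primary outcome section, describe the T0 comparison as agreement across adjacent weeks, bearing on habitual activity, rather than as same-period validity. Then:

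1. Compare the T0 IPAQ with sensor week 1, and report sensor week 1 versus week 2 agreement as the benchmark, on the same activity quantity and with the same statistic. Interpret IPAQ agreement relative to that benchmark.
2. If the 14-day mean is used instead, estimate the week-to-week ICC from the two sensor weeks and derive the cap as ρ / √((1 + ρ)/2).
3. State that the benchmark is approximate: sensor error affects it, and both sensor weeks are monitored, so it does not capture a change in behaviour when monitoring begins.

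This uses only data already collected for everyone enrolled. The cost is a little more analysis and a more modest validity statement.

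Optionally, for any participants still to reach day 16, add the IPAQ items to the questionnaire emailed then and compare them with the overlapping sensor days. The recall would cover about days 9 to 15, of which days 9 to 14 (six of seven) have sensor data. Two limits need stating. This recall follows up to 70 prompts about leisure activity, so it is primed and may agree better than the T0 IPAQ would. And with a planned study end of 6 January 2026 and T2 at 6 months, baselines would have to finish around July 2025 if T2 is to fall within the study, so few or no participants may remain.
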